#### Exclusion criteria

History of severe allergic diathesis; intolerance or contraindications against verapamil, prednisone, pantoprazole or potassium (effervescent tablet); diabetes mellitus (history and screening); cardiac arrhythmia (second and third degree AV block, SA block, sick sinus syndrome, atrial fibrillation, atrial flutter, WPW-Syndrome, bradycardia with HR <50/min); arterial hypotension (systolic pressure <90 mmHg); hypertension (>180 mmHg); history of GIT-ulceration; severe osteoporosis; glaucoma; tuberculosis; current viral (e.g. HSV, VZV, herpetic keratitis) fungal, parasitic or bacterial infections (laboratory screening); poliomyelitis; lymphadenitis following BCG vaccination; acute urinary tract infection; chronic cluster headache; prednisone or verapamil medication less than 30 days before inclusion into the study.

Participation in a different clinical trial less than 30 days before inclusion; previous inclusion into PredCH; parallel participation in a different clinical trial; ongoing substance/alcohol abuse/dependence; history of psychiatric disease with risk of suicide; history of severe chronic or terminal illness; HIV.

Chronic disease which causes impairment of absorption, metabolism, secretion of study medication (e.g. chronic inflammatory bowel disease, renal insufficiency); chronic hepatic disease (lab screening: 2–3 fold increase above normal in liver function test); history of neuromuscular disease (e.g. myasthenia gravis; Duchenne muscular dystrophy, Lambert-Eaton-Syndrome); nursing; pregnancy (pregnancy testing); fertile women with insufficient contraception; absence of consent.

### Excluded therapies and medications

Concomitant medication/nonmedical treatment will be documented.

The following substances cannot be taken during trial, due to possible interactions with study medication: beta antagonists; cardiac glycosides; antiarrhythmic agents (flecainide, disopyramide, quinidine); oral anticoagulants (dabigatran, rivaroxaban, abixaban, vitamin-K antagonists); non-depolarizing neuromuscular blockers; atropine and other anticholinergic agents; praziquantel; chloroquine; hydroxychloroquine; mefloquine; somatotropin; protirelin; inhalational anesthetics; SSRIs and SNRIs; MAO-Is; lithium; laxatives; doxyorubicine; oral antihyperglycemic agents; antacids; indometacin; postmenopausal hormone substitution; colchicine; ethanol; other inhibitors of cytochrome P450 isoenzyme 3A4 such as anti-fungal azoles (e.g. clotrimazole, ketoconazole or itraconazole); protease inhibitors (e.g. ritonavir or indinavir); macrolides; cimetidine; antidepressants; inducers of cytochrome P450 isoenzyme 3A4 such as phenytoin; rifampicin; phenobarbital; carbamazepine; urikosuric agents (sulfinpyrazone); Hypericum perforatum (St John’s wort); benzodiazepines and other anxiolytic agents (e.g. buspirone); substrates of cytochrome P450 isoenzyme 3A4 such as antiarrhythmic agents (e.g. amiodarone); statins (e.g. simvastatin > 20 mg/d or atorvastatin > 40 mg/d); midazolam; ciclosporin, everolimus; sirolimus; tacrolimus; theophylline; prazosin; terazosin.

The following substances which can be used as prophylactic treatment of ECH cannot be taken within 30 days before inclusion into study: methysergide; lithium; topiramate; pizotifen; valproic acid; melatonin; gabapentin.

### Assessment of representativeness

Patients screened for PredCH, who are not included in the study will be registered and documented (date, age, sex, reason for exclusion) in order to assess representativeness of the included patient group.

Patients can always withdraw their consent to participate in the study without stating a reason.

### Statistical analysis and sample size considerations

#### Study populations

All randomized patients who have taken the study medication at least once will be included in the safety assessment group that accords to the treatment group to which they were assigned. Similarly, the intention-to-treat-analysis (ITT) population will be based on patients who have taken the study medication once, but analyses will be done according to randomization allocation. The per-protocol (PP) population excludes patients with protocol violations as defined by the sponsor or the responsible biometrician prior to unblinding.

#### Efficacy

The primary endpoint in the efficacy assessment will be the total number of cluster attacks within the first week of treatment.

The null hypothesis that both intervention groups have the same mean number of attacks will be tested against the (two-sided) alternative hypothesis that there will be a difference in the mean number of attacks between treatment intervention group and placebo group after one week. The confirmatory analysis will be performed in the ITT population.

A generalized linear model will be used to adjust for the stratification variables of sex, age (< 30 years vs. ≥ 30 years) and participating site. The null hypothesis will be rejected when the two-sided p-value of the Wald-test for the intervention group variable is equal or less than the significance level α = 0.05. The average mean difference in the primary endpoint is assumed to be clinically relevant when the mean number of cluster attacks is more than 30% lower in the add-on prednisone group than in the add-on placebo group.

Additionally there will be explorative sensitivity analyses – e.g. in the PP populations. Similarly, secondary endpoints will be analyzed exploratively using appropriate methods of descriptive and inferential statistics. Details will be described in a statistical analysis plan.

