## Background

Episodic cluster headache (ECH) is a primary headache disorder characterized by intense unilateral attacks of facial and head pain lasting between 15 and 180 minutes accompanied by trigemino-autonomic symptoms. The attacks occur between once every other day and eight times per day for an episode lasting between a week and several months. Headache episodes (“inside bouts”) are followed by symptom-free intervals (“outside bouts”) with duration of at least one month. These episodes follow a circadian and circannual rhythm [1].

Therapy for ECH consists of abortive medication such as high flow oxygen, triptans, analgesics or intranasal lidocaine and prophylactic treatment to reduce the number of attacks and quickly end the bout, e.g. verapamil, topiramate or lithium [2-4].

Amongst these, verapamil is regarded as the drug of choice by national and international therapy guidelines. In Germany verapamil is recommended by the “Gemeinsamer Bundesausschuss” (“Federal Joint Committee”) as an off-label-indication (meaning that the treatment is reimbursed by the sick funds). Verapamil has shown efficacy in some randomized controlled studies [5]. Due to its delayed onset of efficacy of usually 10 to 14 days and the required slow titration of the dose to increase tolerability, guidelines recommend initiating short-term prophylactic treatment with overlapping prednisone administration [2-4].

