### Secondary objectives

PredCH will also assess the effect of ± prednisone for the following secondary endpoints:

1. Number of cluster attacks from day 1 to day 28 of study participation.

2. Number of cluster attacks from day 7 to day 28 of study participation.

3. Episode abortion (yes/no), defined as no further attacks in the last 3 days before follow-up on day 7 or day 28.

4. Acute medication intake up till day 7; up till day 28.

5. Responder rate (defined as a reduction in the number of daily attacks >50% measured after 7 and 28 days as compared to mean number of attack during the last three days before inclusion).

6. Presence or absence of trigemino-autonomic symptoms (yes/no) after 7 and 28 days:

a) Lacrimation

b) Nasal congestion, rhino rhea

c) Conjunctival injection

d) Ptosis

e) Miosis

f) Facial sweating on side of pain

7. Impact on quality of life, assessed on day −1 and day 28:

a. SF-12 [34]

b. HIT-6 [35]

c. ADS [36]

8. Pain intensity (mean) of cluster attacks in the first seven days and the first 28 days after initial treatment as measured by the Numerical Rating Scale.

9. Tolerability and safety

a. Adverse events, pathological findings on neurological and medical examination, urinary and blood tests, ECG changes.

b. Drug accountability check on day 7 and day 28

c. CGI [37] on day 7 and day 28, compared to baseline.

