### Visit 0 (baseline)

The study patient will be randomized and study medication will be handed out. The headache diary will be explained to the patient. Screening and randomization can take place on the same day.

### Visit 1

Visit 1 will take place seven days after the baseline visit. A standardized interview will be performed as well as a medical and neurological examination. ECG and vital parameters will be documented. Therapy compliance and the headache diary will be controlled and headache frequency evaluated. Adverse events and dropouts from the study will be documented.

### Visit 2

Visit 2 will be performed 28 days after inclusion. In addition to the tests performed in visit 1, impairment of quality of life will be reassessed (HIT-6, ADS and SF-12) and blood tests will be performed in order to evaluate safety.

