### Randomization/stratification

Randomization will be conducted using a web-based tool “TenALEA”. Patients will be stratified at randomization according to age (<30 years vs. ≥30 years), sex and participating site.

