#### Sample size and power

The sample size calculation is based on the parametric evaluation of a two group comparison using a *t*-test though a more complex statistical model will be used as primary test. Based on data from the literature [5] we estimate the average frequency of headache attacks as 8.25 (with a standard deviation (SD) of 4.2) for 5 days and assume equal SDs in both treatment groups. Requiring α = 0.05 (two-sided) while aiming at a comparison-wise power of 1-β = 0.9 (a higher power was chosen to address the problem that a more complex statistical analysis will be used), a sample size of n = 2 × 61 = 122 patients is necessary for the ITT analysis to detect a mean difference of 2.5 in average frequencies of headache attacks during the first 5 days between treatment by oral prednisone vs. placeobo. In order to address a potential drop-out rate of 15% overall, another 22 patients have to be randomized. Thus, the total maximum sample size is n = 2 × 72 = 144 patients.

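### The primary model leaves out pre-treatment attack frequency, a value the trial needs anyway for its responder endpoint; the cost is precision, not validity

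*Protocol article*

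**What the plan says.** All references are to the protocol article.

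- **Endpoint (Efficacy):** "The primary endpoint in the efficacy assessment will be the total number of cluster attacks within the first week of treatment".
- **Confirmatory model (Efficacy):** "A generalized linear model will be used to adjust for the stratification variables of sex, age" group and participating site, with a two-sided Wald test of the treatment term at 0.05. The covariates are named outright. The reference to a statistical analysis plan comes later, after the sentences on sensitivity analyses and secondary endpoints.
- **Randomization/stratification:** "Patients will be stratified at randomization according to age (<30 years vs. ≥30 years), sex and participating site". Attack frequency is not a factor.
- **Secondary objectives, item 5:** response is a reduction of more than 50% in daily attacks, "as compared to mean number of attack during the last three days before inclusion". A pre-treatment value is therefore needed for every patient.
- **Visit 0 (baseline):** "The headache diary will be explained to the patient. Screening and randomization can take place on the same day".
- **Sample size and power:** "Requiring α = 0.05 (two-sided) while aiming at a comparison-wise power of 1-β = 0.9", with mean 8.25 and SD 4.2 attacks over 5 days, a difference of 2.5, 61 per arm analysed, and 144 randomized to allow for 15% drop-out.

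**The concern.** The outcome is a count of attacks, and the count of the same events just before treatment is a natural predictor of it. Neither the design nor the primary analysis uses that predictor, although the trial must obtain it for a secondary endpoint. Stable differences between patients in attack rate therefore stay in the residual variance: the interval is wider and the power lower than the available data allow. If one arm happens to start with more frequent attacks, the primary estimate is not corrected for it. The covariate has to be named before unblinding, because choosing it afterwards would be open to challenge as data-driven.

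**Working it through.** **1. Reproduce the planned size.** Inputs from Sample size and power: difference 2.5, SD 4.2, two-sided alpha 0.05, power 0.90. The noncentral t calculation gives 61 per arm with power 0.903 (the normal approximation gives 60). Drop-out: 122 / 0.85 = 143.5, rounded up to 144. Both stated figures are correct for an unadjusted t-test.

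**2. Effect of the covariate on the planning scale.** If the baseline correlates r with the outcome, the residual SD is 4.2 × √(1 − r²). The standard error of the difference is that SD × √(2/61). The article gives no r, so a range is assumed. The degree of freedom spent on the covariate is ignored.

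| r | Residual variance, 1 − r² | SE of difference | Power, 61 per arm | Analysed N for 90% power |
|---|---|---|---|---|
| 0 (as planned) | 1.00 | 0.76 | 0.9034 | 122 |
| 0.3 | 0.91 | 0.73 | 0.9276 | 110 |
| 0.5 | 0.75 | 0.66 | 0.9645 | 92 |
| 0.7 | 0.51 | 0.54 | 0.9954 | 64 |

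With an illustrative 50 per arm, power is 0.8382 without the covariate and 0.9255 at r = 0.5.

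**3. A guide to r from the article's own figures.** The variance-to-mean ratio is 4.2² / 8.25 = 2.14, more than Poisson. Assume a gamma-Poisson model in which all the excess is stable variation between patients:

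- k = (4.2² − 8.25) / 8.25² = 0.138; mean daily rate 8.25 / 5 = 1.65; variance of the rate 0.138 × 1.65² = 0.376.
- Variance of a 3-day count: 3 × 1.65 + 9 × 0.376 = 8.33.
- Variance of a 7-day count: 7 × 1.65 + 49 × 0.376 = 29.95.
- Covariance: 21 × 0.376 = 7.89.
- r = 7.89 / √(8.33 × 29.95) = 0.50.

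This value rests on the model. It assumes a stable rate and an accurately counted baseline.

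**4. The actual 7-day endpoint.** The planning SD is for 5 days. With the model-based 7-day SD, √29.95 = 5.47, and a proportional difference of 2.5 × 7/5 = 3.5, power at 61 per arm is 93.9% unadjusted. It becomes 95.7%, 98.1% and 99.8% at r = 0.3, 0.5 and 0.7.

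**5. Simulation with a log link.** Quasi-Poisson regression under the model in step 3, with 61 per arm, 1,500 trials per run, and log of the 3-day count plus 0.5 as covariate:

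- Rate ratio 0.80: power about 72% without the covariate and 83% with it (repeated runs gave 70% to 74% and 81% to 83%). The standard error shrinks to about 0.88 to 0.89 of its size.
- Rate ratio 0.70, close to the design effect (2.5 / 8.25 = 30%): 97.7% and 99.5%.
- Rate ratio 0.80 with a random error of up to ±2 attacks added to the baseline count: 72.5% and 80.5%.
- No effect: rejection between about 5% and 6% either way.

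**6. Chance imbalance.** Under the same model the difference between arms in the mean 3-day count has SD √(8.33 × 2/61) = 0.52. The regression slope of the 7-day count on the 3-day count is 7.89 / 8.33 = 0.95. A typical imbalance therefore moves the 7-day difference by about 0.95 × 0.52 = 0.5 attacks.

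**The case against.** The strongest reply is that nothing here is wrong. The model adjusts for exactly the factors used in stratification, which is coherent. The planned size meets its 90% target without the covariate, and the article says it chose the higher power because the real analysis would be more complex. This stands: the point is about efficiency.

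Four further limits also stand.

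- **Baseline quality.** The diary is first explained at visit 0, and screening may fall on the same day as randomization, so the three-day count may be recalled. The inclusion criteria require a bout that began less than 30 days ago but set no minimum, so the three days may include time before the bout. Both lower r. Neither can bias the comparison, because the value precedes treatment.
- **Size at the design effect.** A reader might take the rise from 72% to 83% as the gain for the planned effect. It belongs to a rate ratio of 0.80. At 0.70 the same simulation gains under 2 points.
- **Spread between patients.** The Background says "The attacks occur between once every other day and eight times per day", and a reader might infer a 16-fold spread within the trial. That is the general range of the disease. Under the model in step 3, patient rates between the 10th and 90th percentiles run from about 0.93 to 2.47 a day, or 2.7-fold.
- **Imbalance.** It does not carry through in full. A slope of 0.95 against 7/3 = 2.33 means about 41% of an observed imbalance reaches the estimate, and the standard error already allows for it on average.

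It can also be said that an analysis plan not shown might add the covariate. That softens the point but does not remove it, because the article states the primary covariates outright and such an addition would change the published confirmatory model.

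**Conclusion.** The point holds as a loss of precision. The primary model omits a prognostic value that the trial needs for its responder endpoint and does not balance by stratification. For an assumed r of 0.3 to 0.7, residual variance is 9% to 49% higher-than-necessary when measured against the unadjusted variance, and power at the design effect could rise from 90% to between about 93% and 99.5% (5-day SD), or from 94% to between about 96% and 99.8% (7-day SD). The practical value is mainly insurance against a smaller true effect or fewer patients than planned.

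A reader might infer that the planned comparison is biased, that its type I error is inflated, or that the trial is too small. The article supports none of these: randomization protects the comparison, and 122 and 144 reproduce exactly for the stated t-test. The size of the gain rests on an assumed correlation. The value of 0.50 also requires a stable attack rate and an accurate baseline count.

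**What to change.** Before unblinding, state in the Efficacy section or the analysis plan that the primary model includes attack frequency over the three days before inclusion as a covariate, beside sex, age group and site. Under a log link, enter it on the log scale, for example log of the 3-day count plus 0.5. Keep the model without it as a prespecified sensitivity analysis. The same covariate would serve the day 1 to 28 count.

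The cost is one sentence. No new data and no further patients are needed, and the sample size can stay as it is.

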#### Safety

Analysis of tolerability and safety will be performed for all patients who took at least one dose of study medication (safety group). During screening and follow up visits patients will participate in a safety assessment which will examine for pathological findings in medical and neurological examination and laboratory tests, abnormal vital parameters, adverse events and suspected adverse effects from study medication. The safety report will analyze differences over time as well as between both intervention groups. Severe adverse events will be reported as single case histories.

#### Sample size and power

The sample size calculation is based on the parametric evaluation of a two group comparison using a *t*-test though a more complex statistical model will be used as primary test. Based on data from the literature [5] we estimate the average frequency of headache attacks as 8.25 (with a standard deviation (SD) of 4.2) for 5 days and assume equal SDs in both treatment groups. Requiring α = 0.05 (two-sided) while aiming at a comparison-wise power of 1-β = 0.9 (a higher power was chosen to address the problem that a more complex statistical analysis will be used), a sample size of n = 2 × 61 = 122 patients is necessary for the ITT analysis to detect a mean difference of 2.5 in average frequencies of headache attacks during the first 5 days between treatment by oral prednisone vs. placeobo. In order to address a potential drop-out rate of 15% overall, another 22 patients have to be randomized. Thus, the total maximum sample size is n = 2 × 72 = 144 patients.

#### Quality assurance/monitoring

The Center for Clinical Trials, Essen (“Zentrum für Klinische Studien Essen” (ZKSE); http://www.zkse.de) will be responsible for the data quality management and monitoring of this trial. As a full member of the national Network of Coordinating Centres for Clinical Trials (KKS Network; http://www.kks-netzwerk.de/), the ZKSE has adapted all harmonized standard operation procedures to the local conditions.

According to the guidelines of GCP, the sponsor is required to select investigators and trial sites as well as review their qualification and the availability of appropriate resources. These will be assessed in a pre-trial visit. The monitor’s report will be distributed to the sponsor, clinical project management and the funding agency. Finally, the sponsor will decide if a site and the related investigators are suitable.

### Informed consent, ethics, data safety monitoring board

#### Informed consent

Prior to inclusion into the study, written informed consent must be obtained from each patient and participation in the trial and written consent will be documented in the patient’s file. The patient must be informed generally about the study, alternative treatment options, risks and benefits from the study, as well as his/her right to withdraw consent.

Each patient who has been entered in the study will receive further prophylactic treatment with verapamil, lithium or topiramate and will be offered a follow-up visit 2 months after the study, even should he/she drop out.

#### Ethics/legal approval

Documented approval has been obtained from the responsible ethics committees at all participating study centers. A list of the responsible ethics committees is provided below. The study conforms to the Declaration of Helsinki, the German legal regulations of the Medicinal Products Act (“Arzneimittelgesetz”) and the current version of the ICH-GCP guidelines.

### Data safety monitoring board

There will be annual controls by the data safety monitoring board, which consists of a neurologist, a cardiologist and a biometrician. This committee will analyze all severe adverse events, infections, drop-outs due to adverse medical effects and mortalities.

## Discussion

PredCH will assess efficacy and safety of prednisone in prophylactic treatment of episodic cluster headache in addition to first line therapy with verapamil in a double-blind controlled trial. Eligible patients will be randomized 1:1 to add-on oral prednisone or add-on placebo with dosages corresponding to international recommendations.

This multi-center trial aims to provide the evidence on efficacy and safety for the initial treatment of ECH, so that patients will be able to receive therapy much faster, both in an in- and outpatient setting. Furthermore, the trial will provide insight into the long-term outcome of ECH after prednisone administration.

## Abbreviations

ADS: Allgemeine Depressionsskala: General Depression Scale – a psychometric self-assessment screening test for depression; CGI: Clinical Global Impression- a scale that helps evaluating effects of therapeutic intervention, regarding severity of disease, improvement efficacy and adverse effects of therapy; ECH: Episodic cluster headache; ECG: Electrocardiogram; GCP: Good Clinical Practice; GIT: Gastrointestinal tract; HIT-6: Headache Impact Test – a six-item questionnaire for screening and monitoring outcomes of patients with headache; HR: Heart rate; HSV: Herpes simplex virus; ICD-10: International Classification of Diseases 10th revision; ICH: International Conference on Harmonisation; IHS: International Headache Society; IMIBE: Institut für Medizinische Informatik, Biometrie und Epidemiologie: Institute for Medical Informatics, Biometrics and Epidemiology; ITT: Intent-to-treat; I.V.: Intravenous administration; MAO-I: Inhibitors of monoamine oxidase; NSAID: Non-steroidal anti-inflammatory drug; PI: Principal investigator; P.O.: Per os, oral administration; SQ: Subcutaneous injection; SF-12: 12-item short form questionnaire: a questionnaire to assess quality of life; SSRI: Selective serotonin reuptake inhibitor; SNRI: Serotonin norephedrine reuptake inhibitor; VZV: Varizella zoster virus; WPW: Wolff-Parkinson-White-syndrome; ZKSE: Zentrum für Klinische Studien Essen: Center for Clinical Trials Essen.

